### Data analysis

#### Statistical analysis

Sociodemographic, clinical, psychosocial and personality variables will be analysed using descriptive and frequency statistics. An intention-to-treat approach will be used. SPSS V24.0 will be used to perform statistical analyses.^44^ An α level of p<0.05 will be used. Analysis of variance and χ tests will be used to assess differences (1) in sociodemographic, clinical and psychological characteristics between the intervention and control groups and (2) in participants and non-participants, as appropriate. Descriptive and frequency statistics will be used to describe the primary outcomes: (1) uptake of genetic counselling and (2) uptake of predictive DNA testing. Logistic regression analysis will be conducted to assess differences between the intervention and control groups on the primary outcomes, with the randomisation group as the main exploratory variable. Two logistic regression models will be used, with the first model including only the randomisation group and the second model also including the potential covariates (ie, sociodemographic, clinical and psychological variables). Multilevel analyses will be performed to assess whether the randomisation group, that is, the independent variable, has an impact on family and psychological functioning, that is, the secondary outcome variables. The two measurement time points in probands will be treated as nested within probands. To prevent influence of potential confounding factors, multilevel analysis will be adjusted for covariates as well. Participant appreciation of the approach used will be described using frequency statistics.

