**Methods:**

A multicentre randomised controlled trial with parallel-group design will be conducted in which an intervention group receiving the tailored approach will be compared with a control group receiving usual care. Adult probands diagnosed with an ICC in whom a likely pathogenic or pathogenic variant is identified will be randomly assigned to the intervention or control group (total sample: n=85 probands). Primary outcomes are uptake of genetic counselling and predictive DNA testing by relatives (total sample: n=340 relatives). Secondary outcomes are appreciation of the approach used and impact on familial and psychological functioning, which will be assessed using questionnaires. Relatives who attend genetic counselling will be asked to fill out a questionnaire as well.

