#### Randomisation

Prior to receiving their test result, probands with an ICC in whom a likely pathogenic or pathogenic variant is identified will be randomly assigned to either the intervention or control group. Block randomisation will be used, with variable blocks ranging from size two to six. Randomisation will be stratified for gender, disease type (cardiomyopathies or primary arrhythmia syndromes) and hospital. To ensure allocation concealment, computer software will be used for randomisation, with an allocation rate of 1:1.^32^ Relatives of probands included in the study will be assigned to the group to which the proband was assigned.

Neither participants nor genetic counsellors will or can be blinded for group assignment. The executing researcher also cannot be blinded because of slight differences between the questionnaires administered in the intervention and control groups. Part of the outcome data will be collected using telephone interviews. To minimise bias, these interviews will be conducted by a research assistant following a structured script.

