### Sample size calculation

The study aims to detect a difference of 15% in uptake of genetic counselling by relatives between the control (usual care, 50%) and intervention groups (tailored approach, 65%). Assuming a two-sided 5% significance level and a power of 80%, 340 relatives (170 in each group) would be required to participate in this study. On average, six relatives per proband are at 50% risk of inheriting the variant, including children and adults.^9^ With a conservative estimate of four eligible adult relatives per proband at risk, 85 probands with an ICC and an identified likely pathogenic or pathogenic (class 4 or 5) variant will need to be included in this study to reach 340 relatives. A likely pathogenic or pathogenic variant is found in, on average, 20% (lower margin) of all probands with a suspected ICC. With an expected response rate of 70% and a drop-out rate of 20%, approximately 759 probands will be approached to participate in the study.

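### Two unranked primary outcomes are both tested at 5% with no decision rule, while the sample size covers counselling uptake only

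*Protocol article*

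**What the plan says.** The abstract already names two primary outcomes: "Primary outcomes are uptake of genetic counselling and predictive DNA testing by relatives". The Primary outcome measures section numbers them (1) and (2) without ranking them, and the Statistical analysis section repeats the pair: "the primary outcomes: (1) uptake of genetic counselling and (2) uptake of predictive DNA testing".

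That section sets one general level, "An α level of p<0.05 will be used", and applies the same method to both outcomes: "Logistic regression analysis will be conducted to assess differences between the intervention and control groups on the primary outcomes". Each outcome is fitted in two models, one with randomisation group alone and one with covariates added. Neither model is named as decisive.

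The Sample size calculation section uses one outcome only: "The study aims to detect a difference of 15% in uptake of genetic counselling by relatives". The rates are 50% under usual care and 65% under the tailored approach, and the result is stated as follows: "Assuming a two-sided 5% significance level and a power of 80%, 340 relatives (170 in each group) would be required". No rate, difference or power is given for testing uptake.

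**The concern.** The article fixes the number of primary outcomes, the significance level and the basis of the sample size, and these three do not fit together. The sizing spends the whole 5% on counselling uptake, yet a second primary outcome is then tested at the same 5%.

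The Objectives section puts counselling and testing into one aim and does not say whether success on one is enough or both are needed. Each reading leaves a gap. If one is enough, the error rate for the primary claim is above the nominal 5%. If both are needed, the error rate is safe but the power for the claim is not the stated 80%. Under either reading, a split result (one outcome significant, the other not) has no agreed interpretation.

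**Working it through.** **Inputs from the article.** Two-sided α = 0.05, power 80%, rates 0.50 and 0.65, 170 relatives per group, 1:1 allocation. Relatives are treated as independent, as the article's own calculation treats them.

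**Assumptions not in the article.** Only counselled relatives are tested, and a share q of them is tested. The article gives no value for q, so a range is shown. The planned measure of conditional uptake, and the separate follow-up of relatives who are counselled but decline testing, indicate that q below 1 is expected.

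**Step 1: reproduce the sample size.** With mean rate 0.575 and pooled variance under the null:

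n = [1.960 × √(2 × 0.575 × 0.425) + 0.842 × √(0.50 × 0.50 + 0.65 × 0.35)]² / 0.15²
= [1.960 × 0.6991 + 0.842 × 0.6910]² / 0.0225 = 169.3, rounded up to 170 per group, 340 in total.

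The stated figure is reproduced exactly, with the full 5% on counselling uptake. At 170 per group the power is 80.2%.

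**Step 2: error rate if either outcome suffices.** Two tests at 5% have an upper bound of 10%, and independent tests give 1 − 0.95² = 9.75%. Here the outcomes overlap, so the excess is smaller. With counselling uptake 0.50 in both groups under the null and testing uptake pt = 0.50q, the correlation of the two outcomes, and so approximately of the two test statistics, is

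ρ = √[pt(1 − 0.50) / (0.50(1 − pt))].

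For q = 0.90: pt = 0.45 and ρ = √(0.225/0.275) = 0.905. The chance that at least one of two standard normal statistics with this correlation exceeds 1.96 in absolute value is 7.0%.

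**Step 3: power for testing uptake.** If q is the same in both arms, the testing rates are 0.50q and 0.65q. For q = 0.80 they are 0.40 and 0.52, with mean 0.46:

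power = Φ[(0.12 × √170 − 1.960 × √(2 × 0.46 × 0.54)) / √(0.40 × 0.60 + 0.52 × 0.48)]
= Φ[(1.565 − 1.381)/0.700] = Φ(0.262) = 60%.

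| Share q tested | ρ | At least one false positive | Testing difference (points) | Power for testing uptake |
|---|---|---|---|---|
| 50% | 0.58 | 8.8% | 7.5 | 33% |
| 70% | 0.73 | 8.2% | 10.5 | 51% |
| 80% | 0.82 | 7.7% | 12.0 | 60% |
| 90% | 0.90 | 7.0% | 13.5 | 70% |
| 95% | 0.95 | 6.4% | 14.25 | 75% |

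At q = 100% the two outcomes coincide and the error is 5%. Power for significance on both outcomes cannot exceed the power for testing uptake alone, so the last column is an upper limit under a rule that both must succeed.

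**Step 4: compare remedies.** Splitting α into 0.025 for each outcome would cut counselling power at 170 per group from 80% to 71%. Restoring 80% would take 206 per group (412 relatives). A fixed sequence needs neither: testing uptake is examined only after counselling uptake is significant at 5%, so the two tests add no error beyond that 5%, and 340 relatives still suffice for counselling uptake.

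**The case against.** The strongest objection is that an order or adjustment for two primary outcomes is often left to the analysis plan, which is not at hand, and that a general 5% level does not exclude one. This stands in part: such a plan could supply the rule, so confidence is moderate. It does not dispose of the point, because the article itself fixes two primaries, one flat level and a calculation that spends the whole level on one of them. A later α split would undercut the published power.

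Second, a reader might infer that the article lets success on either outcome carry the claim. It does not say so. The single aim could equally be read as requiring both, in which case no α adjustment is needed. The 6% to 9% is therefore conditional on the either-outcome reading.

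Third, a reader might infer that a 15-point gain in counselling must be a smaller gain in testing. Nesting alone does not imply this; it needs equal tested shares in both arms. With 85% tested in control and 90% in intervention, the testing rates are 0.425 and 0.585, a gain of 16 points with power of about 84%. The 60% to 75% is thus an illustration under equal shares.

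Fourth, a reader might add in the clustering of relatives within families and quote a much larger error. Most of that excess would arise with a single outcome. With four relatives per family and an assumed intracluster correlation of 0.10, the variance inflation is 1 + 3 × 0.10 = 1.3, and one unadjusted test already has an error of 2[1 − Φ(1.96/√1.3)], about 8.6%. That is a separate matter, which a fixed sequence would not cure, and it is not counted here.

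**Conclusion.** The point holds in conditional form. The article states no decision rule for two primary outcomes tested at the same 5%, and its sample size supports only one of them.

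- If either outcome suffices, the family-wise error is about 6% to 9%. This rests on 50% counselling uptake, 50% to 95% of counselled relatives tested, testing only after counselling, and independent relatives. The direction (above 5%) holds whenever some counselled relatives are not tested.
- If both are required, the 80% power does not cover the claim. Power for testing uptake is about 60% to 75% for tested shares of 80% to 95%, equal in both arms.

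The inflation is modest because the outcomes overlap. Running an unadjusted and an adjusted model for each outcome, with neither named as primary, adds a further route to a false positive that these figures leave out. Nothing here requires testing uptake to lose its primary status.

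**What to change.** State a fixed sequence. Counselling uptake, the powered outcome, is tested first at two-sided 5%. Testing uptake is tested at two-sided 5% only if counselling uptake is significant. Name in advance one model, the same for both outcomes, on which these tests rest. State in the sample size section that the 80% power applies to counselling uptake only. Both outcomes may remain primary.

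The sample size and the power for counselling uptake do not change. The price is that testing uptake cannot be claimed alone if counselling uptake is not significant. The trial is registered and the Trial status section reports 68 probands already randomised, so the change needs a documented amendment, made before outcome data are analysed.

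### The primary logistic models for uptake have no family term although whole families are allocated through the proband, so the test is too liberal under any positive within-family correlation

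*Protocol article*

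**What the plan says.** All four statements are in the Methods of the protocol article.

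- **Randomisation.** Probands are randomised 1:1, and "Relatives of probands included in the study will be assigned to the group to which the proband was assigned". The family is therefore the unit of allocation.
- **Primary outcome measures.** Uptake counts the relatives counselled, and the relatives tested, against all eligible relatives in the pedigree. The section adds that uptake is to be measured by arm and at the level of the family, but attaches no test to this.
- **Statistical analysis.** "Logistic regression analysis will be conducted to assess differences between the intervention and control groups on the primary outcomes". The first model contains the randomised group only, and the second adds sociodemographic, clinical and psychological covariates. Multilevel analysis is named for family and psychological functioning, which are secondary outcomes. The one nesting described is this: "The two measurement time points in probands will be treated as nested within probands".
- **Sample size calculation.** The target is 65% uptake against 50% under usual care. "Assuming a two-sided 5% significance level and a power of 80%, 340 relatives (170 in each group) would be required to participate in this study". The number of families follows by division: "With a conservative estimate of four eligible adult relatives per proband at risk, 85 probands". Neither an intracluster correlation nor a design effect appears.

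**The concern.** Randomisation is by family and the analysis is by relative, so for uptake this is a cluster-randomised comparison. A logistic regression without a family term treats four relatives of one proband as if they had been randomised separately. If relatives of the same proband tend to attend or stay away together, the data carry less information than 340 independent observations. The model's standard errors are then too small, its confidence intervals too narrow, and its false-positive rate above the stated 5%.

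Such correlation is plausible here. Relatives of one proband share a diagnosis in the family, a letter, and above all the person through whom, or with whose consent, they are informed. The Introduction gives reasons why a proband may not inform relatives, or not inform them correctly. Several of these, such as grief or poor understanding of the importance of the information, could affect several relatives at once. At stake is the test of both primary outcomes.

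**Working it through.** **Inputs from the article.** Uptake 50% and 65%; two-sided 5% level; 80% power; 170 relatives per arm; four relatives per proband; 85 probands.

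**Input assumed.** The intracluster correlation, written ρ here because the article uses ICC for inherited cardiac conditions. The documents give no value, so I use 0.05 to 0.30.

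**1. Reproduce the plan's figure.** Two independent proportions, pooled variance, no continuity correction, mean proportion 0.575:

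n per arm = [1.96 × √(2 × 0.575 × 0.425) + 0.842 × √(0.50 × 0.50 + 0.65 × 0.35)]² / 0.15² = 169.3, rounded up to 170.

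This matches 170 per arm and 340 in total, with power 80.2%. Then 340 / 4 = 85 probands. The match is exact with no allowance for clustering, so independence is built into the planned numbers as well as the model.

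**2. Effect of clustering.** With equal families of size m = 4:

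- Design effect: DE = 1 + (m − 1)ρ = 1 + 3ρ.
- Actual type I error of the unadjusted test: 2 × [1 − Φ(1.96 / √DE)].
- Shortfall in interval width: 1 − 1/√DE.
- Power of a test that allows for clustering: the two-proportion power at 170/DE per arm.

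| ρ (assumed) | DE | √DE | Actual type I error | Interval too narrow by | 170/DE | Adjusted power at 340 relatives | Relatives (probands) for 80% power |
|---|---|---|---|---|---|---|---|
| 0 | 1.00 | 1.00 | 5.0% | 0% | 170 | 80% | 340 (85) |
| 0.05 | 1.15 | 1.07 | 6.8% | 7% | 147.8 | 74% | 392 (98) |
| 0.10 | 1.30 | 1.14 | 8.6% | 12% | 130.8 | 69% | 442 (111) |
| 0.20 | 1.60 | 1.26 | 12.1% | 21% | 106.3 | 60% | 544 (136) |
| 0.30 | 1.90 | 1.38 | 15.5% | 27% | 89.5 | 53% | 646 (162) |

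**3. Check by simulation.** Beta-binomial families of four, 42 against 43 families, 50% uptake in both arms, unadjusted logistic Wald test, 20,000 runs. The rejection rate was 4.6% at ρ = 0, then 6.1%, 8.4%, 11.6% and 15.1% at 0.05, 0.10, 0.20 and 0.30. This agrees with the formula.

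**4. Sensitivity to family size.**

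- *Larger families.* The sample size section also says: "On average, six relatives per proband are at 50% risk of inheriting the variant, including children and adults". The primary outcome counts eligible children too. With m = 6, the type I error is 8.0%, 11.0% and 16.6% at ρ = 0.05, 0.10 and 0.20. The power picture improves, because 85 families would then supply 510 relatives: adjusted power is 87%, 80%, 68% and 58% over the four values of ρ.
- *Unequal families.* DE becomes 1 + [(1 + CV²)m − 1]ρ, where CV is the coefficient of variation of family size. If size is taken as 1 + Poisson(3), which is my assumption, CV² = 3/16 = 0.1875 and DE = 1 + 3.75ρ. The type I error is then about 7.2%, 9.5%, 13.8% and 17.9%.

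**The case against.** **A statistical analysis plan, not shown here, may add a family term, and an article condenses.** This would be decisive if the article had only named logistic regression. It goes further: it lists the terms of both primary models, names multilevel methods for other outcomes, and sizes the trial as if relatives were independent. That is a stated choice, and it needs correcting even if another document differs.

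**The authors knew of the family level, because uptake is to be measured there.** True, but that sentence describes measurement and names no model or variance. Logistic regression on family counts (relatives attending out of relatives eligible) has the same binomial likelihood, so without an overdispersion or cluster term its standard errors are just as small.

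**Covariates in the second model may absorb the correlation.** Only the part they explain, and the first model has none.

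**Within-family correlation is not shown.** This stands in part. A reader might infer from the Introduction that outcomes within a family must be correlated. The text is more guarded: it says that some relatives decline deliberately, that many others may be unaware, and that uptake is around 50% even though most relatives received a letter from the proband. In the intervention arm the counsellor also writes directly to relatives for whom the proband consents. Positive correlation is plausible, not established, and its size is unknown.

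**The relatives' questionnaire outcomes.** A reader might infer that they have the same fault, since the only nesting named is time within probands. The article does not support that. It plans multilevel analysis for family and psychological functioning, which are measured in relatives too, and relatives complete one questionnaire, so time cannot be their nesting level. The text does not exclude a family level there. It is silent, and an article may leave that detail to the analysis plan.

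**Conclusion.** The point holds for both primary outcomes and both stated models. Allocation is by family, while the models and the sample size treat relatives as independent, so the test exceeds its nominal level for any positive within-family correlation. At zero correlation there is no error.

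The size rests on an assumed correlation. With equal families of four and values from 0.05 to 0.30, the type I error is about 6.8% to 15.5% and intervals are 7% to 27% too narrow. At the lower end the excess is under two percentage points; at the upper end the error rate is about three times nominal. Larger or unequal families raise it further. The values up to 17.9% depend on a family-size distribution that the documents do not give, so they serve as sensitivity figures only.

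This should be corrected before the analysis, because it concerns the main test of the trial.

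**What to change.** In the Statistical analysis section, state that both logistic models, for counselling and for DNA testing, account for clustering by proband family. A random intercept for family would do, as would GEE or a cluster-robust variance with proband as cluster and a small-sample correction. Any of these is acceptable, provided one is named as primary in advance. Report the observed intracluster correlation for each outcome.

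No new data are needed, since each relative is already linked to a proband. The change can be fixed in advance: under Trial status the article reports 68 probands randomised and data collection continuing until January 2020.

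The cost should be stated openly. Confidence intervals will widen, and with 340 relatives in families of four the power is about 74%, 69%, 60% and 53% at correlations of 0.05, 0.10, 0.20 and 0.30. The Sample size calculation should restate the 80% figure with an assumed correlation and family size. If recruitment cannot be extended, the lower power should be acknowledged.

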Some relatives who do not attend genetic counselling will have deliberately decided against predictive DNA testing. However, the low uptake percentages also suggest that many relatives may be unaware, or insufficiently aware, of the risks involved and/or the possibilities for genetic counselling and subsequent surveillance and treatment. This is supported by research on family communication in ICCs. Patients are not always able to inform or correctly inform their relatives for a number of reasons, including disengagement with relatives, lack of understanding of the importance of the information, preoccupation with their own grief, difficulties in conveying the complex information to relatives or a wish to prevent burdening relatives by informing them about genetic risks.^8 14–18^

Previous studies assessing interventions to enhance family communication in hereditary diseases showed that some interventions are effective in increasing the uptake of genetic counselling.^19–21^ An intervention trial aimed at improving family communication in specifically dilated cardiomyopathy is still ongoing.^22^ A few studies have been published on more active approaches to informing relatives at risk in which healthcare professionals (HCPs) contact at-risk relatives directly.^23–26^ These studies suggest that a more active approach can almost double the uptake of genetic counselling and predictive DNA testing by relatives. However, some of these studies were performed in a research setting (eg, in relatives already registered in research databases for the genetic disease), hampering direct translation of these results to a diagnostic setting. To our knowledge, more active approaches in patients with ICCs have not been studied thus far. However, a study by Ormondroyd *et al*
14 suggests that relatives eligible for predictive DNA testing for hypertrophic cardiomyopathy and long QT syndrome would support a more active approach to informing relatives at risk.

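### The trial is planned on a 15-point difference in uptake, but the models stated for the primary outcomes give no such difference with a confidence interval and, as stated, ignore allocation by family

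*Protocol article*

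**What the plan says.** **Planning scale.** Under Sample size calculation: "The study aims to detect a difference of 15% in uptake of genetic counselling by relatives", from 50% under usual care to 65% under the tailored approach, at a two-sided 5% level and 80% power. On this basis, "340 relatives (170 in each group) would be required to participate in this study". Under Primary outcome measures, the effect is likewise described as the difference between the groups in uptake of counselling and of DNA testing.

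**Analysis.** Under Statistical analysis, both primary outcomes are first described with frequencies. Then: "Logistic regression analysis will be conducted to assess differences between the intervention and control groups on the primary outcomes". There are two models, one with randomisation group only and one that adds sociodemographic, clinical and psychological covariates. No effect measure is named and no interval for the difference in uptake is mentioned. Multilevel models are stated for the secondary outcomes only, where the two time points are nested within probands.

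**Allocation.** Under Randomisation, probands are allocated 1:1 and relatives take their proband's group. The sample size section counts four eligible adult relatives per proband.

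**The concern.** The design question is how many more relatives in 100 come forward, and the trial is sized to detect 15. The usual output of a logistic model is an odds ratio, which does not answer that question directly. Three consequences follow.

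- **Reading the number.** Uptake of 50% to 65% is common, so the odds ratio lies well above the ratio of uptakes. A reader who takes one for the other gets the wrong size of effect.
- **Comparing the two models.** Odds ratios are non-collapsible. When there is a true effect and the covariates predict uptake, the adjusted odds ratio lies further from 1 than the unadjusted one even if the covariates are perfectly balanced. Side by side, the gap can be mistaken for confounding that adjustment has removed.
- **Precision.** Relatives in one family share an allocation and probably resemble one another. A model with no family term treats them as independent, and its intervals will be too narrow if uptake is positively correlated within families. Readers cannot repair this from the described percentages, because a valid interval needs the family-level data.

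**Working it through.** **Inputs.** Uptake 50% and 65%, two-sided 5%, 80% power, 170 relatives per group and four relatives per proband (Sample size calculation); 1:1 allocation of probands, with relatives following (Randomisation). The covariate standard deviations and the intracluster correlations (ICC) are assumptions, because the article gives neither.

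**1. The plan's own figure.** Two proportions, pooled variance, no continuity correction, mean uptake 0.575:

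n per group = [1.960 × √(2 × 0.575 × 0.425) + 0.8416 × √(0.50 × 0.50 + 0.65 × 0.35)]² / 0.15² = (1.370 + 0.582)² / 0.0225 = 169.3, rounded up to 170, so 340 in total. The figure reproduces, and it rests on the absolute difference.

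**2. The planned effect on three scales.**
- Difference: 0.65 − 0.50 = 0.15.
- Uptake ratio: 0.65 / 0.50 = 1.30.
- Odds ratio: (0.65 / 0.35) / (0.50 / 0.50) = 1.857.

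Read as an uptake ratio, 1.86 would turn a 30% relative increase into one of 86%.

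**3. Does the scale cost power?** Treating relatives as independent, 170 per group gives 80.2% for the comparison of proportions. For the unadjusted logistic Wald test, the variance of the log odds ratio is 1/(170 × 0.25) + 1/(170 × 0.65 × 0.35) = 0.04939, so its standard error is 0.2222. Then 0.6190 / 0.2222 − 1.960 = 0.826, and power is 79.5%. The scale makes almost no difference to the test.

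**4. Unadjusted against adjusted odds ratio without confounding.** Let logit(uptake) = a_g + s·X, with X standard normal and identically distributed in both groups. Solve for a_0 and a_1 so that uptake averaged over X is exactly 50% and 65%. The adjusted odds ratio is exp(a_1 − a_0).

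| Assumed SD s on the logit scale | Adjusted odds ratio | Standardised difference |
|---|---|---|
| 0 (unadjusted) | 1.86 | 0.150 |
| 0.5 | 1.92 | 0.150 |
| 1.0 | 2.11 | 0.150 |
| 1.5 | 2.39 | 0.150 |

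The odds ratio moves while the effect on uptake does not.

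**5. Width of the interval for the difference.** With independent relatives the standard error is √(0.2500/170 + 0.2275/170) = 0.0530, so the 95% half-width is 1.96 × 0.0530 = 10.4 points. With four relatives per family the design effect is 1 + 3 × ICC.
- ICC 0.05: design effect 1.15; half-width 10.39 × √1.15 = 11.1 points.
- ICC 0.20: design effect 1.60; half-width 10.39 × √1.60 = 13.1 points.

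**The case against.** The strongest reply is that the article contains no error here. It never mentions odds ratios. It names a model and leaves the effect measure open, which a condensed article may leave to a fuller document, and a logistic model can produce a standardised difference. Uptake will be described by group, so the crude difference and the crude ratio can both be seen. The unadjusted model tests the same null hypothesis as the planning comparison. Reporting unadjusted and adjusted logistic models side by side is ordinary practice, and each odds ratio is a valid quantity.

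Most of this stands, and it limits the point to estimation and reporting. It does not remove it. The section sets out the method, the number of models, their content and the software, and within that account nothing yields an interval for the quantity on which the trial was sized. Nor do the models as described contain a family term.

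Three stronger readings are tempting, and the document does not support them.
- A reader might infer that logistic regression is the trial's only inferential analysis. That is true of the group effect on the primary outcomes only; multilevel models are stated for the secondary outcomes.
- A reader might infer that odds ratios overstate the effect. At the planned rates 1.86 is the correct odds ratio. It misleads only if read as a ratio of uptakes, and the article does not say that it will be.
- A reader might take the Introduction's remark that "a more active approach can almost double the uptake of genetic counselling and predictive DNA testing by relatives" as the trial's benchmark. It is background on earlier studies, and the same paragraph cautions that some of them transfer poorly to a diagnostic setting. The trial's target is 15 points.

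**Conclusion.** The point holds as an inexpensive improvement to estimation and reporting. It is not an error in the stated figures: 340 relatives reproduces, and the choice of scale leaves the null hypothesis unchanged and nominal power nearly so.

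The gap between an odds ratio of 1.86 and an uptake ratio of 1.30 follows from the planned rates alone. The shift to between 1.92 and 2.39 depends on the assumed covariate strength, and with weak covariates it is small. It also assumes covariates that allocation cannot have changed. The article collects probands' characteristics at T1, one month after the result, so a variable that could respond to allocation would not meet that condition.

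The half-widths of 11.1 to 13.1 points, against 10.4, depend on the assumed ICC and on equal families of four. The power figures treat relatives as independent. Correlation within families would lower power on either scale, but that is a sample-size question separate from this one.

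**What to change.** Add to Statistical analysis, for both primary outcomes: the absolute difference in uptake between the groups will also be reported with a 95% confidence interval. It will be standardised from the logistic model (average predicted uptake with everyone set to intervention, minus the average with everyone set to control), with standard errors clustered by the proband's family or obtained by resampling whole families. Unadjusted and adjusted results will be compared on this scale. Odds ratios may stay alongside, with their intervals clustered in the same way.

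The cost is a sentence or two of text and a short post-estimation step, possibly outside the SPSS menus. The intervals will be somewhat wider than those from a model that ignores families. No new data are needed, and this change does not itself alter the sample size.
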